## **2.7 Sensitivity analyses of the primary outcome**

### **2.7.1 Adjusted analyses**

The logistic regression model described in Section 2.6.1 will be re-run after adjustment for the following covariates: gender, age (continuous), ED diagnosis, day of ED presentation, ED mode of arrival and ATS category.

### **2.7.2 Analysis including the intervention period**

A secondary exploratory analysis will be performed including the implementation period into the intervention group (see definition in Section 1.1). This analysis will be performed both unadjusted and adjusted; however, no subgroup analysis will be applied.

## **2.8 Analysis of secondary outcomes**

### **2.8.1 Binary outcomes**

All binary secondary outcomes will be analysed using the same strategy as the one applied to the primary outcome, that is using both an unadjusted and adjusted logistic regression model and both by excluding and including the intervention period, thus giving four models. Subgroup analyses will not be conducted on secondary outcomes.

### **2.8.2 Continuous outcomes**

Continuous outcomes such as time in ED, will be analysed using the same strategy as the binary outcomes; however, logistic regression will be replaced with linear regression (normal distribution and an identity link function) and the effect of the intervention will be estimated as the modelled mean difference and its 95% CI.

### **2.8.3 Patient reported outcomes**

All patient reported outcomes will be treated as continuous outcomes and therefore analysed following the strategy described in Section 2.8.2.

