| Lumbar radiculopathy (disorder)                                               | 128196005 |
| Sciatica (disorder)                                                           | 23056005  |
| Spinal stenosis of lumbar region (disorder)                                   | 18347007  |

Patient-reported outcomes were collected using automated text messaging at one week (primary time point) and again at two and four weeks after index ED presentation. Between July 2018 and December 2018, all eligible patients presenting to the participating EDs were invited to complete a brief self-reported online survey at ED discharge. Reminder messages were sent to non-responders, and those who did not respond to the reminder message were contacted via telephone. We invited a total of 807 eligible patients and 416 (52%) agreed to participate and completed week-1 survey. Of those, 360 (87%) completed week-2 and 351 (84%) week-4 surveys.

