### **2.1 Analysis principles**

- Data analysis will be performed according to an intention-to-treat analysis, that is, clusters will be analysed according to their randomised cross-over time irrespective of whether cross-over was achieved at the desired time.
- All tests are to be two-sided with a nominal level of  $\alpha$  set at 5%.
- Subgroup analyses (see Section 2.5.3) will be carried out irrespective of whether there is a significant treatment effect on the primary outcome. These analyses will also be unadjusted.
- No formal adjustments for multiplicity will be applied. However, the outcomes will be categorised by the degree of importance (primary vs secondary), and only a limited number of subgroup analyses are pre-specified. The results will be interpreted in this context.
- Analyses will be conducted primarily using SAS software (version 9.3 or above).

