## 2.6 Analysis of the primary outcome

### 2.6.1 Main analysis

The primary endpoint is a binary variable indicating whether a patient received any lumbar imaging (yes/no). The primary analysis will be conducted using a logistic regression with a random effect for cluster (hospital ED), a random effect for clinician nested within cluster, a fixed effect indicating the group assignment of each cluster at each step and a fixed effect of time (each step). The model will be specified as follows:

$$\text{logit} [ P(Y_{ijk} = 1) ] = \alpha + \beta \text{Group}_{ij} + \delta_j + u_i + v_{ijk} + e_{ijk} \quad (1)$$

where:

- $Y_{ijk}$  denotes the outcome of subject  $k$  ( $k=1, \dots, m_{ij}$ ) in period  $j$  ( $j=1, 2$ ) within ED  $i$  ( $i=1, \dots, N$ ) where  $m_{ij}$  indicates the number of subjects in period  $j$  within ED  $i$
- $\alpha$  is the intercept
- $\text{Group}_{ij}$  is a dummy variable indicating group allocation during period  $j$  for cluster  $i$  with  $\text{Group}_{ij} = 1$  post-intervention, and  $\text{Group}_{ij} = 0$  pre-intervention
- $\beta$  is the parameter of interest estimating the treatment effect and where  $e^\beta$  is the odds ratio (OR)
- $\delta_j$  is a fixed period effect
- $u_i$  is a random cluster effect with  $u_i \sim N(0, \sigma_u^2)$

$v_{ijk}$  is a random clinician effect which is nested within cluster with  $v_{ijk} \sim N(0, \sigma_v^2)$   
 $e_{ijk}$  are individual-level errors following a binomial distribution

The effect of the intervention will be presented as the OR of receiving any lumbar imaging and its 95% confidence interval (CI). In case of convergence issues caused by the inclusion of two random effects, we will remove the random clinician effect and keep the random cluster effect.

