### **2.6.2 Treatment of missing data**

Given the ED dataset only records lumbar images that occurred, we will assume that a missing data point indicates that the corresponding procedure did not occur. The primary outcome (i.e. lumbar imaging) will therefore not contain any missing data. However, manual data extraction from patient's medical records were conducted for some secondary outcomes (i.e. opioid medication), since some EDs did not have electronic medication system (eMEDS) available. No imputation of secondary or patient reported outcomes will be performed.

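### Patient-reported outcomes at weeks 1, 2 and 4 go through a one-record-per-patient model, so the supportive week-2 and week-4 contrasts ignore the week-1 scores of patients who stopped responding

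*Combined protocol and SAP*

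**What the plan says.** SAP 1.3 has patient-reported outcomes collected "at one week (primary time point) and again at two and four weeks after index ED presentation". On response it reports: "We invited a total of 807 eligible patients and 416 (52%) agreed to participate and completed week-1 survey". It continues: "Of those, 360 (87%) completed week-2 and 351 (84%) week-4 surveys". Later respondents are therefore subsets of the week-1 respondents.

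The analysis text in SAP 2.8.3 is one sentence: "All patient reported outcomes will be treated as continuous outcomes and therefore analysed following the strategy described in Section 2.8.2". Section 2.8.2 takes over the strategy for binary outcomes with a linear model in place of the logistic one, and that strategy is the primary-outcome model of 2.6.1. The model is described as having "a random effect for cluster (hospital ED), a random effect for clinician nested within cluster, a fixed effect indicating the group assignment", plus a fixed effect of time. Its outcome carries three indices (ED, trial period, subject). The time term is the trial period, not the survey week.

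On missing data, SAP 2.6.2 states: "No imputation of secondary or patient reported outcomes will be performed".

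**The concern.** Three surveys per patient are sent to a model that has room for one. The SAP does not say how weeks 2 and 4 enter it. The reading that fits the model's indices is a separate fit at each week. Under that reading, a patient who answered at week 1 but not at week 4 drops out of the week-4 analysis, although the best available predictor of the missing score is in the dataset.

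At stake are the supportive later contrasts for the SAP 1.2 objective that patient outcomes are not worse. SAP 1.3.3 sets a 1-point margin for pain. If patients with more pain at week 1 stop responding more often in one condition than in the other, the respondents-only difference at weeks 2 and 4 shifts for reasons unrelated to the intervention. With imputation excluded, only a model that uses the earlier scores directly can correct for this.

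**Working it through.** **Inputs.** From SAP 1.3: 807 invited; 416, 360 and 351 respondents at weeks 1, 2 and 4. From SAP 1.3.3: margin 1, SD 2.5, ICC 0.05, 80% power, 30 per ED per period, five periods, four EDs. From SAP 2.1: two-sided 5%. Assumed: correlation r between surveys of 0.5–0.7, equal for every pair of weeks.

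**1. The plan's own figure.** The Hussey–Hughes variance for I = 4 EDs and T = 5 periods, one ED crossing per period, is

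Var = I·s·(s + T·t) / [(I·U − W)·s + (U² + I·T·U − T·W − I·V)·t], with U = 10, W = 30, V = 30.

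Taking 2.5 as the total SD, t = 0.05 × 6.25 = 0.3125. With 30 per cell, s = 5.9375/30 = 0.1979. Then Var = 4 × 0.1979 × 1.7604 / (1.979 + 9.375) = 0.1227, so SE = 0.350. Power = Φ(1/0.350 − 1.96) = 81.4%, and 29 per cell suffice for 80%. The stated 30 per cell (600 overall) is therefore reproduced by a calculation with one record per patient.

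**2. Who is lost.** 416/807 = 51.5%, so 391 never responded. Week 2: 416 − 360 = 56 (13.5%). Week 4: 416 − 351 = 65 (15.6%).

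**3. Precision.** A joint likelihood was compared with separate fits through the information matrix, summing the inverse correlation matrix over response patterns. The number answering all three surveys is not given. It must lie between 360 + 351 − 416 = 295 and 351, and the ranges below cover that whole interval.

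| Assumed r | Week 1: SE separate/joint | Week 2 | Week 4 |
|---|---|---|---|
| 0.5 | 1.000 | 1.017–1.023 | 1.021–1.027 |
| 0.7 | 1.000 | 1.035–1.041 | 1.042–1.048 |

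Separate fits therefore cost about 2–5% in SE at weeks 2 and 4, and nothing at week 1.

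For power, use the simpler effective size n_eff = n/[1 − r²(1 − n/416)], which borrows from week 1 only, in the formula of step 1:

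- Week 1: 416, power 67.3%, unchanged.
- Week 2: 360 becomes 373–385; power 61.5% becomes 62.9–64.2%.
- Week 4: 351 becomes 365–380; power 60.5% becomes 62.1–63.7%.

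These powers assume equal cells in the layout of SAP 1.3.3 and take no account of the implementation weeks that SAP 2.2 leaves out of the analysis. Only the changes matter here.

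**4. Bias.** This is a two-group simulation with 208 per group, SD 2.5, no true difference, and r of 0.5–0.7 as above plus 0.9. All dropout rules are assumed.

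- *Dropout tied to week-1 pain in one group only* (log-odds −1.75, plus 0.3 per point in that group; about 16% missing). The respondents-only week-4 difference is off by 0.15, 0.21 and 0.27 points at r = 0.5, 0.7 and 0.9. This is r times a shift of about 0.30 in the mean week-1 score of those who remain. The group losing its high-pain patients looks better than it is. An estimate that uses the week-1 score has bias of about 0.00.
- *The same dropout rule in both groups.* Bias is about 0.00 with no true effect, and at most about 0.07 points with a true 1-point effect.

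Against the 1-point margin, bias of 0.15–0.21 (r = 0.5–0.7) is material but needs differential dropout. Under a common rule it is small.

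**The case against.** The case for leaving the plan alone is substantial.

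- **Week 1 is the named primary time point, and every participant has it.** This stands. The joint model gains nothing there, so the shortfall of 416 against the planned 600 is not eased.
- **Separate fits at supportive time points with 84–87% retention are conventional, and the precision gain is small.** This also stands. Precision alone would hardly justify the change.
- **Bias in the group contrast needs dropout that differs between conditions, and no document shows that.** This is correct. A reader might infer that separate fits are valid only if dropout is unrelated to week-1 scores. That is too strong, because a common dropout rule leaves the contrast essentially unbiased. Differential dropout remains plausible: clinicians are unblinded (protocol, Intervention) and patient education is part of the package (protocol Appendix 3). Once the model is specified, guarding against it requires no new data.

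Two larger figures are tempting and should not be used. Stacking the surveys without a patient effect would give an SE 1/√(1 + 2r) = 0.71–0.65 of the correct one, that is 29–36% too small. However, the model indexes one outcome per subject, so the SAP does not describe stacking. Likewise, averaging the three surveys would give an SE roughly 9–17% below week 1 alone at r = 0.5–0.7. That average is an estimand the plan never names, so it is not a gain on the planned one.

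**Conclusion.** The point holds as a cheap improvement to the supportive analyses. SAP 2.8.3 sends repeated measurements to a model without repeated-measures structure, and 2.6.2 closes the other route to using the earlier scores. Read week by week, which is an inference from the model's indices, weeks 2 and 4 discard information on 56 and 65 patients. The certain cost is an SE about 2–5% too large, given the assumed r of 0.5–0.7. The possible cost is bias in those two contrasts: 0.15–0.21 points at the same r under one illustrative pattern of differential dropout, and close to zero if both conditions lose patients in the same way.

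A reader might infer that the primary patient-reported result is compromised, or that a repeated-measures model would repair the 52% response. Neither follows. Week 1 is unaffected, and no earlier patient-reported score is described for the 391 non-respondents. The protection at weeks 2 and 4 also depends on dropout being missing at random given the observed scores.

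**What to change.** In SAP 2.8.3, for pain intensity, physical function and quality of life, specify one linear mixed model on weeks 1, 2 and 4 with:

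- a patient random effect or unstructured within-patient covariance;
- survey week and group-by-week;
- additive trial-period effects;
- the existing ED and clinician terms, keeping the 2.6.1 rule that the clinician effect is dropped if the model does not converge.

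Report week 1 as the primary contrast and weeks 2 and 4 as supportive. State that validity rests on missing at random given the observed scores, and that the three surveys will not be stacked without a within-patient term. A 4-week average is optional; if added, label it as a new estimand. Satisfaction concerns a single ED visit, so it can stay outside this model.

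The cost is a few sentences and no new data. The downside is a somewhat heavier model with more risk of non-convergence: 416 patients over 4 EDs and 5 periods is about 21 per cell (416/20). That is why the period effects are kept additive rather than crossed with survey week.
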